## Abstract

**Background:**

Patients with stroke often experience reduced cardiorespiratory fitness, which increases the risk of cardiovascular events, and conventional rehabilitation has limited efficacy in improving it. Transcutaneous auricular vagus nerve stimulation (taVNS) can modulate autonomic function, but its effect on cardiorespiratory fitness in stroke patients remains unclear.

**Methods:**

This randomized controlled trial will enroll 160 patients with subacute stroke, who will be randomly assigned in a 1:1 ratio to an experimental group or a control group. Both groups will receive conventional rehabilitation training. The experimental group will additionally receive active taVNS (left auricular concha, 25 Hz, 200 µs, intensity set at or slightly above the sensory threshold, 30 min/session, 5 sessions/week for 4 weeks), while the control group will receive sham stimulation (0 mA). The primary outcome is set as peak oxygen uptake (VO_2_peak), assessed at baseline (T0), post-intervention (T1), and follow-up (T2). Secondary outcomes include: (1) inflammatory markers (IL-6, TNF-α); (2) neurological function (National Institutes of Health Stroke Scale, NIHSS); and (3) activities of daily living (modified Barthel Index, MBI), all measured at T0, T1, and T2. Resting-state electrocardiogram (5 min) will be recorded at T0, T1, and T2 to analyze heart rate variability (HRV) as an exploratory outcome to elucidate autonomic mechanisms, without multiplicity correction. Data will be analyzed following the intention-to-treat principle.

**Discussion:**

This protocol aims to investigate the effect of taVNS on cardiorespiratory fitness in patients with subacute stroke.

## Introduction

Stroke is a leading cause of disability and mortality among adults in China, imposing a substantial burden on society and families due to its high incidence. Patients in the subacute phase often face multiple functional impairments, among which the decline in cardiorespiratory fitness has received insufficient attention (1). This decline stems not only from stroke-induced damage to central autonomic regulation (2) and cardiac function (3), but also from secondary prolonged bed rest and physical inactivity (4, 5). Cardiorespiratory fitness, with peak oxygen uptake (VO_2_peak) as its core indicator, is a powerful predictor of overall functional reserve (6). For stroke survivors, low cardiorespiratory fitness not only hinders the recovery of motor function and activities of daily living but is also associated with adverse cardiovascular prognosis (7, 8). Therefore, identifying effective rehabilitation interventions to improve cardiorespiratory fitness in patients with subacute stroke has become a noteworthy issue in this field.

High-intensity exercise is an effective means of improving cardiorespiratory fitness (9). However, common functional impairments following a stroke often prevent patients from achieving the required exercise intensity. In recent years, transcutaneous auricular vagus nerve stimulation (taVNS), a non-invasive neuromodulation technique, has gained widespread attention due to its safety and efficacy. Its theoretical basis lies in the superficial distribution of the auricular branch of the vagus nerve in the auricular concha. Low-intensity electrical stimulation in this area can antidromically activate the vagus nerve, modulate key brainstem nuclei such as the nucleus tractus solitarius, and optimize autonomic nervous system function (10, 11). Preliminary studies have suggested the potential of taVNS in improving post-stroke cognitive and motor functions, as well as in treating conditions such as epilepsy and depression (12–17). Mechanistically, taVNS may, by modulating autonomic function, improve cardiac chronotropic function and reduce inflammatory responses, thereby enhancing cardiorespiratory fitness (18, 19). However, no high-quality randomized controlled trial to date has specifically investigated the effect of taVNS on cardiorespiratory fitness in stroke patients.

To accurately assess cardiorespiratory fitness, this study adopts the internationally recognized cardiopulmonary exercise test (CPET) (20). CPET provides a comprehensive evaluation of the integrated function of the heart, lungs, and skeletal muscles by simultaneously monitoring gas exchange under progressively increasing exercise loads, with VO_2_peak as its core measure (21). Under close supervision, CPET can be safely performed in patients with subacute stroke to precisely quantify the degree of cardiorespiratory impairment and the efficacy of interventions.

This study aims to systematically evaluate, through a methodologically rigorous randomized controlled trial, the effects of a 4-week taVNS intervention combined with conventional rehabilitation training on cardiorespiratory fitness in patients with subacute stroke. We hypothesize that, compared with the sham stimulation control group, active taVNS will significantly improve VO_2_peak, along with favorable changes in heart rate variability, inflammatory markers, and neurological function.

Notably, cardiovascular events are a leading cause of death among stroke survivors (22). The field of neurocardiology emphasizes the bidirectional interactions between the brain and the heart. Cardiorespiratory fitness, as a powerful predictor of cardiovascular outcomes (6), may serve as an integrative marker linking neurological recovery and cardiac prognosis after stroke.

## Methods

### Study design

This study is a randomized, sham-controlled, parallel-group superiority trial. The study procedures and schedule are detailed in Table 1 (Study schedule and assessment timeline) and Figure 1 (Anticipated participant flow diagram).

**Table 1 T1:** Study schedule and assessment timeline.

Item	Assessment point T0 (Baseline)	Intervention phase (weeks 1–4)	Assessment point T1 (end of intervention)	Follow-up phase (weeks 5–8)	Assessment point T2 (follow-up assessment)
Time correspondence	Week 0	← 4 weeks →	End of Week 4	← 4 weeks →	End of Week 8
Enrollment and allocation					
Participant screening	●				
Informed consent	●				
Demographic data collection	●				
Medical history and medication record	●				
Randomization	●				
Intervention					
Experimental group (active taVNS)		●			
Control group (sham stimulation)		●			
Conventional rehabilitation training		●		●	
Primary outcome					
Cardiopulmonary exercise testing (VO_2_peak)	●		●		●
Secondary outcomes					
Inflammatory markers (IL-6, TNF-α)	●		●		●
NIHSS score	●		●		●
Modified Barthel index	●		●		●
Exploratory outcome					
Heart rate variability (SDNN, HF)^1^	●		●		●
Safety assessment					
Adverse event recording		●	●	●	●
Serious adverse event reporting		●			
Compliance monitoring					
Treatment session completion record		●	●		
Others					
Concomitant medication record	●	●	●	●	●
Unblinding request record		●	●	●	●

1 Heart rate variability (HRV), as an exploratory outcome, will be analyzed from 5 min resting-state electrocardiograms recorded before cardiopulmonary exercise testing at T0, T1, and T2. It will not be subjected to multiplicity correction and will be used only for explanatory analyses. T0 = baseline assessment point (pre-intervention assessment and randomization); T1 = post-intervention assessment point (end of week 4); T2 = follow-up assessment point (end of week 8). The intervention phase spans weeks 1–4, and the follow-up phase spans weeks 5–8. The symbol “●” indicates that the procedure or assessment is performed at the corresponding time point.

**Figure 1 F1:**
[figure not shown]
Anticipated participant flow diagram (CONSORT framework). T0 = baseline assessment point; T1 = post-intervention assessment point (end of week 4); T2 = follow-up assessment point (end of week 8). During the follow-up period (weeks 5–8), no electrical stimulation is delivered; only conventional rehabilitation is maintained. The final report will include the actual numbers of participants screened, excluded, randomized, lost to follow-up, and included in each analysis.

### Participant recruitment

Participants will be recruited consecutively from July 2026 to June 2027. Recruitment sources will include patients attending the Neurorehabilitation Center of Shaanxi Rehabilitation Hospital and community-dwelling stroke survivors recruited from relevant communities in Xi'an City.

### Diagnostic criteria

The diagnosis of stroke will conform to the World Health Organization (WHO) definition. All cases must be confirmed as acute ischemic or hemorrhagic stroke by cranial computed tomography (CT) or magnetic resonance imaging (MRI). The diagnosis will be independently verified by at least two specialist neurologists.

### Inclusion criteria

(1)Age 40–75 years;(2)First-ever stroke, disease duration 1–6 months;(3)Presence of definite lower limb hemiparesis: Brunnstrom stage ≥II in the affected lower limb, with or without upper limb involvement;(4)Clinically stable condition, stable vital signs, and clear consciousness;(5)Possess the minimum motor function required to complete cardiopulmonary exercise testing: be able to perform a pedaling motion in a seated position, have a muscle strength of the affected lower limb ≥grade 3, and be capable of safely completing cycle ergometer-based cardiopulmonary exercise testing;(6)Voluntary provision of written informed consent.

### Exclusion criteria

(1)Presence of severe cardiac dysfunction (LVEF < 40% or NYHA class ≥ III), hepatic dysfunction (ALT/AST > 3 × upper limit of normal), or renal dysfunction (eGFR < 30 mL/min/1.73 m^2^); uncontrolled hypertension (resting systolic blood pressure ≥180 mmHg or diastolic blood pressure ≥110 mmHg); unstable angina, recent (<3 months) myocardial infarction, symptomatic valvular heart disease, atrial fibrillation, high-risk ventricular arrhythmias, second-degree type II or higher atrioventricular block, or symptomatic bradycardia (<45 bpm); acute coronary syndrome; chronic obstructive pulmonary disease; or active infection.(2)Presence of severe mental illness or cognitive impairment;(3)Skin lesions, infection, or deformity of the ear;(4)Affected lower limb muscle strength ≤grade 2, and inability to complete cycle ergometer-based cardiopulmonary exercise testing;(5)Presence of implanted electronic medical devices (including pacemakers, implantable cardioverter-defibrillators, neurostimulators, deep brain stimulators, and other active implantable electronic devices), as they may be susceptible to electrical interference or cannot be safely used in the taVNS environment;(6)Current participation in other clinical trials that may interfere with the outcomes of this study.

### Screening procedures

This study plans to recruit 160 participants with subacute stroke from the Neurorehabilitation Center of Shaanxi Rehabilitation Hospital and community-dwelling stroke survivors in Xi'an. All potential participants must have their clinical diagnosis independently confirmed by at least two neurologists according to the diagnostic criteria of the WHO and the American Heart Association/American Stroke Association (AHA/ASA), and confirmed by cranial CT or MRI. Additionally, participants must present with definite lower limb hemiparesis (Brunnstrom stage ≥II in the affected lower limb), with or without upper limb involvement. Individuals passing the initial screening will undergo a systematic baseline evaluation conducted by a trained research coordinator. This evaluation includes assessments of motor function, autonomic symptoms, and safety screening for cardiopulmonary exercise testing. Eligibility will be finalized by checking against the inclusion and exclusion criteria checklist. All potential participants will undergo systematic screening for CPET contraindications before enrollment, including medical history and physical examination. If pulmonary embolism or deep vein thrombosis is suspected, further investigations (e.g., four-limb deep venous ultrasound, pulmonary CTA) will be performed to ensure CPET safety.

### Discontinuation and withdrawal criteria

Participants will discontinue treatment or be withdrawn from the study if any of the following occur:
(1)Occurrence of a serious adverse event that, in the investigator's judgment, makes continued participation inappropriate. Such participants will discontinue treatment, but their available data will still be included in the intention-to-treat analysis;(2)Participant voluntarily withdraws informed consent and requests withdrawal. Such participants will be withdrawn from the study, and all data collection will cease;(3)Poor adherence: The actual number of completed intervention sessions is less than 80% of the planned number. Such participants will discontinue treatment but will still be encouraged to continue participating in subsequent follow-up assessments, and their data will be included in the intention-to-treat analysis;(4)Receipt of other interventions during the study period that may affect the outcome measures. Such participants will discontinue treatment, but their available data will still be included in the intention-to-treat analysis;(5)Loss to follow-up (missed two consecutive scheduled visits or unable to be contacted). Such participants will not be considered as having actively withdrawn from the study; their available data will be included in the intention-to-treat analysis, and missing data will be handled using multiple imputation.

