### Intervention

A transcutaneous auricular vagus nerve stimulation device manufactured by Jiangxi Jingyi Medical Technology Co., Ltd., China, will be used. Stimulation electrodes will be placed over the vagus nerve distribution hotspot in the left auricular concha (23, 24). The stimulation parameters are: biphasic square wave, frequency 25 Hz, pulse width 200 µs, single session duration 30 min (25). The stimulation intensity will be individually adjusted based on each participant's sensory threshold. The sensory threshold is defined as the minimum current intensity at which the participant first clearly perceives a tingling sensation on the skin surface (starting from 0.1 mA and increasing slowly). The stimulation intensity in the active taVNS group will be set at a level that is just at or slightly above the sensory threshold (i.e., an intensity that the participant can clearly perceive without pain), typically between 0.5 and 1.5 mA, to ensure a clear, comfortable, and non-painful stimulation sensation. Treatment will be administered once daily, five days per week, for a total of 4 weeks. The sham stimulation group will use the same device, electrode placement, and operational procedures as the active stimulation group. Consistent with previous studies (25), the stimulation current will be set to 0 mA throughout the entire 30 min session. The indicator lights and buzzer sounds of the device will be synchronized with those of the active stimulation group throughout the treatment period.

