Both groups will receive standardized conventional rehabilitation training delivered by the same rehabilitation team during the intervention period (weeks 1–4), consisting of 4 weeks, 5 days per week. The training includes: physical therapy (once daily, 40 min): positioning and transfer training (5 min), affected lower limb weight-bearing training (10 min), sit-to-stand transfer training (10 min), balance training (10 min), and walking training (5 min); and occupational therapy (once daily, 30 min): activities of daily living training (e.g., dressing, eating, grooming) and upper limb functional training. All training will be supervised one-on-one by uniformly trained therapists. Training intensity will be assessed every 5 days according to the patient's Brunnstrom stage and modified Barthel Index score, following an individualized progression principle. Training performance will be recorded in a standardized training log and reviewed weekly by the study coordinator. Adjustments to the duration of individual modules based on the patient's functional characteristics are permitted, provided the total duration remains unchanged; however, adding or removing training modules is not allowed. During the follow-up period (weeks 5–8), participants will continue to receive the same conventional rehabilitation training as in the intervention period (with unchanged content, frequency, and supervision), but will no longer receive taVNS or sham stimulation. Training performance will continue to be recorded and reviewed.

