### Sample size calculation

The sample size for this study was estimated based on the group-by-time interaction effect for the primary outcome, VO_2_peak. Given the current lack of direct prior data on the effect of taVNS on VO_2_peak in stroke patients, we referred to the standardized effect size (*d* = 0.58) reported in a randomized controlled trial in healthy populations (25). Considering the greater heterogeneity in stroke patients, a conservative moderate effect size assumption was adopted for sample size planning. The sample size calculation was based on the group-by-time interaction from repeated-measures ANOVA, while the primary analysis will use a linear mixed-effects model; the two approaches are consistent in their handling of repeated-measures data, and LMM is more robust to missing data, so the sample size adequacy is unaffected. *A priori* power analysis was performed using the *F* tests—ANOVA: Repeated measures, between–within interaction module in G * Power 3.1 software, with the following parameters: effect size *f* = 0.25, *α* = 0.05, power (1 − *β*) = 0.80, number of groups = 2, number of measurements = 3, correlation among repeated measures = 0.50, and non-sphericity correction *ε* = 0.75. The effect size conversion was based on the formula *f* = *d*/2 (for two-group comparisons), with *d* = 0.58 (healthy populations) converted to *f* = 0.25 (stroke patients). A conservative estimate was adopted considering the greater heterogeneity expected in stroke patients. The assumed correlation among repeated measures (*ρ* = 0.50) was based on the typical range (0.3–0.7) reported in similar stroke rehabilitation studies, taking the median value; the non-sphericity correction (*ε* = 0.75) was set as a conservative value recommended by the G * Power software manual. Under these assumptions, the required total sample size was estimated to be approximately 128 participants, i.e., approximately 64 per group. Accounting for a 20% dropout rate, a final sample size of 160 participants (80 per group) was planned. Given the current lack of direct data on the effect of taVNS on VO_2_peak in stroke patients, this study adopted a conservative estimate based on the effect size from healthy populations; future research may further define the clinically meaningful difference in this population.

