### Quality control and assurance

All research personnel will receive unified training before the trial commences. The inter-rater reliability, assessed by the intraclass correlation coefficient for scale assessments, must reach ≥0.85 before personnel can participate in formal evaluations. Data entry will employ a double-entry verification mechanism. The research coordinator will be responsible for ongoing data monitoring and review, conducting monthly data integrity checks. At least three neurology and cardiology specialists will jointly supervise the enrollment assessment and diagnostic process. To protect participant privacy, only the research team members, ethics committee, and relevant regulatory authorities will have access to participants' personal information and medical records.

Adherence monitoring: Adherence to rehabilitation training will be monitored using the same threshold as for taVNS/sham stimulation (≥80% of planned sessions), and will be recorded separately from the intervention adherence.

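### Falling below 80% of stimulation sessions triggers a non-safety treatment stop that either withholds deliverable dose from participants kept in the ITT analysis or does nothing (low severity)

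*Protocol article*

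**What the plan says.** Under Discontinuation and withdrawal criteria, item (3) states: "Poor adherence: The actual number of completed intervention sessions is less than 80% of the planned number. Such participants will discontinue treatment". It adds that these participants will "still be encouraged to continue participating in subsequent follow-up assessments, and their data will be included in the intention-to-treat analysis". Unlike item (1), on serious adverse events, it leaves nothing to the investigator's judgment.

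The Intervention section sets the schedule: "Treatment will be administered once daily, five days per week, for a total of 4 weeks". For weeks 5 to 8 it says that participants continue rehabilitation "but will no longer receive taVNS or sham stimulation".

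Under Quality control and assurance, the same figure appears as a monitoring measure: "Adherence to rehabilitation training will be monitored using the same threshold as for taVNS/sham stimulation". Rehabilitation adherence is recorded separately, and no stop is attached to it there.

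The article does not say when the 80% is judged or whether missed sessions can be made up. The one per-protocol exclusion that it spells out (Cardiopulmonary exercise testing) rests on test effort, not on session count. The treatment stop is therefore the only stated consequence of the 80% stimulation threshold.

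**The concern.** A stopping rule should protect the participant or the estimate, and this one does neither. Serious adverse events are handled by item (1) and by Adverse event monitoring. The data are kept and the participant stays in the ITT analysis. What remains is an instruction to give less treatment to someone who has already had too little.

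The primary effect is the baseline-adjusted group difference at T1 among all randomized participants. If the effect of active stimulation rises with dose, withholding active sessions for non-safety reasons pulls that difference toward zero. Sham sessions deliver 0 mA, so stopping them removes no current. At stake is an avoidable loss of dose in a superiority trial, with nothing gained in return.

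**Working it through.** **Threshold.** Planned sessions: 5 per week × 4 weeks = 20. 80% of 20 = 16. Four misses are allowed; with no make-up sessions, the fifth puts 16 out of reach. The rule cannot be a running count against 16, because everyone is below 16 until the sixteenth completed session.

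**Reading A: applied during the course, at the fifth miss.** If the fifth miss falls at scheduled session k, the participant has received k − 5 sessions and the rule withholds the remaining 20 − k. Without the rule, up to 15 could be received.

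| Fifth miss at session | Received | Withheld |
|---|---|---|
| 5 | 0 | 15 |
| 10 (all of week 2 missed) | 5 | 10 |
| 15 (all of week 3 missed) | 10 | 5 |
| 20 (all of week 4 missed) | 15 | 0 |

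**Reading B: applied at the end of week 4.** No stimulation is scheduled afterwards, so nothing is withheld.

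**Average size under reading A.** The documents give no miss rate. Assume independent misses with probability p per session and no make-up sessions. Then P(fifth miss at k) = C(k−1, 4) p⁵ (1−p)^(k−5), summed over k = 5 to 20. Lost dose per arm member = P(stopped) × mean remaining sessions × (1−p). Expected delivered dose without the rule = 20(1−p).

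| | p = 0.05 | p = 0.10 | p = 0.15 |
|---|---|---|---|
| P(stopped) | 0.0026 | 0.0432 | 0.1702 |
| Stopped, of 80 | 0.2 | 3.5 | 13.6 |
| Mean sessions received at stop | 12.15 | 11.73 | 11.21 |
| Mean sessions remaining | 2.85 | 3.27 | 3.79 |
| Of these, would be attended | 2.70 | 2.94 | 3.22 |
| Mean loss per arm member (sessions) | 0.007 | 0.127 | 0.548 |
| Expected sessions without the rule | 19.0 | 18.0 | 17.0 |
| Relative loss | 0.04% | 0.71% | 3.23% |

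**Effect on power.** Sample size calculation gives f = 0.25 and f = d/2, so d = 2 × 0.25 = 0.50. It also says that the "required total sample size was estimated to be approximately 128 participants, i.e., approximately 64 per group". A two-sided two-sample t-test at α = 0.05 with 64 per group and d = 0.50 has power 0.801. If the effect is proportional to dose, d becomes 0.50 × (1 − relative loss):

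| | No rule | p = 0.05 | p = 0.10 | p = 0.15 |
|---|---|---|---|---|
| d | 0.500 | 0.4998 | 0.4965 | 0.4839 |
| Power, unadjusted | 0.801 | 0.801 | 0.796 | 0.775 |
| Power, baseline-adjusted | 0.900 | 0.900 | 0.896 | 0.880 |

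The last row takes the planned correlation of 0.50 and divides d by √(1 − 0.50²) = √0.75. It is closer to the planned primary analysis, which adjusts for baseline.

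**The case against.** The strongest reply is that the harmless reading is at least as natural. Item (3) compares a completed number with a planned number, which sounds like a final tally. Table 1 marks the session completion record at T1 as well as during weeks 1 to 4. Judged then, the phrase is redundant and costs nothing. This stands as a real possibility. It is not conclusive, because an instruction to discontinue treatment suggests that treatment is still running.

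Second, the fifth-miss trigger and the absence of make-up sessions are assumptions, and a condensed article commonly leaves such operational detail to the full protocol. That is fair, and with make-up sessions the fifth miss need not decide the matter. But the point is not the missing timing. The stated consequence is unhelpful whichever timing is chosen.

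Third, the numbers are small. That is right. Only the assumed 15% miss rate produces a visible change, and with baseline adjustment power stays at 0.880. The model also assumes that stopped participants would attend their remaining sessions at the average rate. They may attend fewer, which would shrink the loss. Clustered misses could instead raise the number stopped. The documents settle neither.

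Fourth, stopping sham sessions may not be neutral. Allocation and blinding itself raises expectancy as a possible influence on exercise-test performance, so losing sham sessions could remove an expectancy benefit and work against dilution. This also stands, and it is why the direction can be called likely but not certain.

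A reader might infer that poor adherers are dropped from the analysis, or that the rule seriously underpowers the trial. The documents support neither. Follow-up is encouraged and ITT inclusion is explicit, and under the assumptions shown the power loss is at most a few percentage points.

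**Conclusion.** The point holds at low severity. Criterion (3) is an automatic, non-safety stop below 16 of 20 sessions for participants who remain in the ITT analysis. Nothing else in the article softens it or says when it applies. It either withholds sessions that could be given or has no effect, and in neither case does it help the trial.

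The size is not given by the documents and is probably small on average: zero under the end-of-course reading, and 0.04% to 3.2% of delivered dose under the in-course reading. The latter range rests on independent misses at 5% to 15%, no make-up sessions, and remaining sessions attended at the same rate; the power figures add an effect proportional to dose. One participant can lose much more, for example 10 sessions after missing all of week 2. The net shift in the T1 contrast is likely to be toward no difference, subject to the expectancy caveat. There is no post-randomization exclusion and no sign of bias toward a false positive result.

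**What to change.** In criterion (3), replace the treatment stop with a recorded adherence flag at 80% of planned sessions, usable for the per-protocol sensitivity analysis. This matches how the protocol already treats rehabilitation adherence. State that participants may resume their remaining scheduled sessions unless there is a safety reason to stop or they decline. Keep the follow-up assessments, the ITT inclusion and criterion (1) as they are.

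The cost is one sentence, with no extra visits, data or participants. Ethics and dissemination describes the changes to sample size and analysis as made before enrollment, with recruitment planned from July 2026, so the edit can be made before the rule is used. The downside is that some participants will continue with incomplete courses.
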